## Abstract

The prevalence of cognitive impairment in hemodialysis (HD) patients is extremely high. Despite the well-documented benefits of interventions on cognitive function, there is a widespread call for effective strategies that will show the long-term consequences in patients undergoing dialysis. The aim of this research protocol was to investigate the effect of cognitive training combined with physical exercise on cognitive function, physical performance, and frailty indicators in the HD population. We will conduct a randomized controlled intervention trial to examine the effects of a combined non-pharmacological intervention in the form of intradialytic physical exercise and intradialytic cognitive training on cognitive function, indicators of frailty, and physical performance measures in HD patients. The group of patients receiving the study intervention will be compared to the control group receiving standard HD care. The duration of the intervention will be 12 weeks. We will use sensitive instruments (cognitive domain tests) to assess cognitive functions. The primary outcome of the study at 12 weeks will be performance on the Alertness subtest of the computerized Test of Attentional Performance. Secondary study outcomes are: Performance in other domains of cognitive function (executive function, psychomotor speed, information processing efficiency, working memory, and attention), physical fitness (10 repetition sit-to-stand test, timed up and go test, handgrip strength test, spontaneous gait speed, and stork balance test), and assessment of frailty (Edmonton Frail Scale). Study outcomes will be assessed at baseline, immediately after the 12-week intervention, and 6 months after the end of the study without specific further intervention (retention effect assessment). This study will be among the first to test the synergistic effects of a uniquely designed physical exercise and cognitive training intervention on functional status in HD patients. We believe our results will contribute to dementia prevention research by demonstrating the long-term efficacy of our combined intervention.

**Clinical Trial Registration:**
ClinicalTrials.Gov, NCT05150444.

## Introduction

The number of older adults is increasing worldwide, as mortality at younger ages is decreasing (World Report on Ageing and Health, 2015). In addition, 50 million people suffer from dementia, and experts predict that this number will increase to 152 million by 2050 (Patterson, 2018). Dementia affects not only the sufferers themselves, but also their families and caregivers, and represents a global economic burden (Abbott, 2011). To date, no effective pharmacological drug has been developed to reverse dementia, and the side effects of symptom alleviating drugs may not outweigh their benefits (Perneczky, 2019), therefore non-pharmacological approaches are highly needed to prevent cognitive decline and consequential dementia. Physical exercise and cognitive training have been suggested as possible strategies to protect against dementia (Livingston et al., 2020).

Most of the physical exercise and cognitive training intervention studies have been delivered in the general population. Much less is known about these effects in the population of patients with chronic diseases, in whom the disease itself and its treatment may increase the risk of cognitive decline and dementia. Patients with chronic kidney disease (CKD) are a typical example since they often suffer from hypertension, diabetes, cardiovascular diseases, and frailty that pose a risk for cognitive decline and dementia (Livingston et al., 2020; Viggiano et al., 2020). The prevalence of cognitive impairment in hemodialysis (HD) is estimated to be 30–60% (Fazekas et al., 1995; Sehgal et al., 1997; Madan et al., 2007). McAdams-Demarco et al. (2018a) found that the 10-year risk of developing dementia after starting HD is 19% in patients aged 66–70 years and increases to 28% in patients aged 76–80 years. Cognitive dysfunction also correlates with frailty in HD patients (McAdams-Demarco et al., 2015; Shen et al., 2017). A recent systematic review with meta-analysis found that the prevalence of frailty in HD patients is 46% (Lee and Son, 2021). The above findings suggest that preventive interventions are needed. Only a few studies have examined the impact of exercise programs on the preservation of cognitive function in HD patients. A 6-month home-based personalized walking exercise program in adult dialysis patients showed significant improvement in self-reported cognitive function score and quality of social interaction score compared to the control inactive group (Manfredini et al., 2017). The limitation of this study is that they used the self-reported Kidney Disease Quality of Life Short Form (KDQOL-SF), which was found in the study by Sorensen et al. (2012), as a poor indicator of neurocognitive performance in HD patients due to insufficient sensitivity. Clearly, the usage of more objective and specific measurement tools is needed.

In another study, 12 HD patients performed 3 months of tablet-based cognitive training (n-back training) during dialysis and showed improvements in Mini-Mental State Exam (MMSE) scores, Montreal Cognitive Assessment (MoCA) scores, and executive function (Noguchi et al., 2020). Limitations here were a small sample size with no control group and a significant probability of a learning effect due to the nature of used tests. McAdams-Demarco et al. (2018b) conducted a pilot study with 20 HD patients randomly assigned to a 3-month intradialytic cycling program (*n* = 6), 3-month intradialytic tablet-based brain games (*n* = 7), and a standard care control group (*n* = 7). The results showed a decrease in psychomotor speed and executive function in the control group, while the decrease was not found in the other two groups. This result is promising and it justifies the execution of larger randomized interventional studies with a better balance of confounding factors in study groups.

Considering the general lack of research in this area, the above-mentioned limitations of recent studies, aging of the CKD population and the burden of cognitive decline and frailty, further well-designed studies with non-pharmacological interventions are clearly needed. Combined cognitive and exercise training aimed at improving cognitive and executive function has been implemented and tested in the general elderly population (Colcombe et al., 2006; Levine et al., 2007; Hill et al., 2017; Jonasson et al., 2017; Butler et al., 2018) but not in HD patients. There are many unanswered questions in the dialysis population, which we aim to address in this research protocol. Therefore, the following research questions were identified:

i. What is the effect of non-pharmacological interventions in the form of combination physical exercise and cognitive training on cognitive function in HD patients?ii. By using the combination of physical exercise and cognitive training is it possible to reduce the level of frailty in HD patients?iii. What is the long-term effect of a short-term intervention in the form of physical exercise and cognitive training on cognitive and physical functioning in HD patients?

The study purpose is to investigate the effect of cognitive training combined with physical exercise on cognitive function, physical performance, and frailty indicators in the HD population.

## Materials and Methods

We will conduct a randomized, controlled interventional trial to examine the effects of intradialytic physical exercise in combination with intradialysis cognitive training on cognitive function, frailty indicators, and physical performance measures in population of HD patients. Main study outcome will be score on of the Test of Attentional Performance (TAP). The duration and frequency of the intervention in the form of intradialytic cycling and tablet-based cognitive training will be 12 weeks, 3 days a week. The comparator group will be HD patients under standard care, receiving only general advice on physical exercise benefits.

### Participants

Participants will be recruited from the dialysis center in University Medical Centre Ljubljana. Inclusion criteria, exclusion criteria, and withdrawal criteria for the study are listed in Table 1.

**Table 1 tab1:** Study criteria.

Inclusion criteria	Exclusion criteria	Withdrawal criteria
HD replacement therapy >3 months	Active malignant or infectious disease	Any intercurrent illness or trauma that prevents the patient from continuing the intervention for a period longer than 14 days
Over 18 years old	Uncontrolled arterial hypertension	The occurrence of an acute illness lasting longer than 3 weeks or ending less than 3 weeks before the end of the study
Stable medical condition	Angina pectoris of Canadian Cardiovascular Society grade 2–4	Diagnosis of a malignant disease throughout the research
Able to walk independently	New York Heart Association heart failure grade 3 or 4	Cerebrovascular or other cardiovascular event (new-onset angina pectoris, myocardial infarction, symptomatic peripheral arterial obliterative disease, heart failure hospitalization)
	Severe cognitive impairment and dementia	Withdrawal of consent to participate
	History of limb amputation	
	Any other condition that could cause the patient to be clinically unstable	

HD, hemodialysis.

The study will be conducted in accordance with the ethical standards of the 1964 Declaration of Helsinki and has been approved by the Slovenian Medical Ethical Committee (number 0120-474/2021/4). Participants will sign an informed consent form before participating in the study. The study was registered at ClinicalTrials.gov under NCT05150444.

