### Statistical Methods Including Sample Size Calculation

The primary outcome of this study will be the cognitive function assessed with the subtest “Alertness” of the Test for Attentional Performance (TAP, Version 2.3; Psytest, 2012).

The sample size was calculated using G*Power software (version 3.1; Faul et al., 2009) on the basis of the results of the study by Briken et al. (2014). For the calculation, the scores of the subtest alertness from the TAP test battery which were obtained from the group that completed bicycle ergometry before (376.91 ± 151.67) and after (302.64 ± 83.09) the treatment were used. The alpha error probability was set to 0.05, the 1-beta error probability to 0.80, while the effect size was taken from the previously mentioned research (0.314). A sample size of 22 participants was calculated. Allowing for a 20% attrition rate, a total number of 27 participants is required, with 14 participants assigned to each group. Analyses will be conducted according to the intention-to-treat principle.

SPSS 24.0 (SPSS, Inc., Chicago, IL, United States) software will be used for all calculations. All data will be presented with mean ± standard deviation and 95% confidence intervals when appropriate. Normality will be confirmed by using the Shapiro–Wilk test, with additional Q–Q plot visual inspection. Independent-sample *t* test, *χ*^2^, or Mann–Whitney tests will be used to determine group differences in clinical and demographic variables, depending on the comparison and test assumptions. The main effects will be analyzed using a mixed general linear model (GLM), taking into account the groups (EXP and CON) and time (baseline and after 12 weeks) as factors. After determining the interaction effect, a secondary analysis will be used to determine the time effect in both groups. Additionally, the degree of effect will be determined for dependent variables by using partial eta-squared (*η*^2^). Partial eta squared readings of 0.02, 0.13, and 0.33 were rated differences as small, moderate, and high (Pierce et al., 2004). Furthermore, in the case of unmatched baseline means, the analysis of covariance (ANCOVA) with baseline measurements entered as a covariate will be applied. For non-parametric data, a Friedman ANOVA will be applied, followed by a Sign-test separately for each scale. Statistical significance will be set at values of *p* < 0.05.

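### Table 1 withdraws randomised patients from the study for health reasons, one row can apply only to the training arm, and this is not reconciled with intention-to-treat

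*Protocol article*

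**What the plan says.** All references are to the protocol article.

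- **Participants, Table 1.** The table is introduced as giving the withdrawal criteria for the study, not for the training. Row 1 is "Any intercurrent illness or trauma that prevents the patient from continuing the intervention for a period longer than 14 days". Row 2 is "The occurrence of an acute illness lasting longer than 3 weeks or ending less than 3 weeks before the end of the study". Rows 3 to 5 are a new malignancy, a cerebrovascular or other cardiovascular event, and withdrawn consent.
- **Study Interventions and Protocol.** Patients are randomised 1:1 after the baseline measurements. EXP trains three times a week for 12 weeks; CON receives standard haemodialysis care.
- **Procedures.** The named risk of taking part is that physical exertion may worsen health.
- **Statistical Methods Including Sample Size Calculation.** "Analyses will be conducted according to the intention-to-treat principle". The main model is a mixed general linear model in SPSS with group and two times (baseline, 12 weeks), reported with partial eta-squared. The calculated 22 patients become 27 for 20% attrition, with 14 per group.

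**The concern.** Every Table 1 withdrawal happens after randomisation, and four of the five rows are health events that may be related to cognition and physical function. Intention-to-treat keeps such patients in the comparison. A rule that takes them out of the study works against that, and one that can take them out of only one arm can unbalance groups that randomisation had balanced.

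Two features sharpen the point. Row 1 covers trauma as well as illness, so it could remove EXP patients hurt by the training itself. Row 2 reaches patients who have already recovered. The Abstract places the retention visit 6 months after the end of the study, so that end appears to be the 12-week point. Withdrawing a recovered patient shortly before then makes sense mainly as a way to leave out the primary measurement.

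At stake is whether the 12-week contrast compares the groups as randomised, in a trial with only 14 patients per arm.

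**Working it through.** **1. Who is withdrawn under Table 1, read literally**

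| Event | EXP | CON |
|---|---|---|
| Illness stopping training for 15 to 21 days, over at least 3 weeks before study end | withdrawn (row 1) | stays |
| Trauma stopping training for more than 14 days | withdrawn (row 1) | no matching row |
| Acute illness longer than 3 weeks | withdrawn | withdrawn (row 2) |
| Acute illness ending in the last 3 weeks | withdrawn | withdrawn (row 2) |
| Malignancy, cardiovascular event, withdrawn consent | withdrawn | withdrawn |

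The asymmetry is confined to the first two lines.

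**2. The plan's own sample size**

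Inputs: "The alpha error probability was set to 0.05, the 1-beta error probability to 0.80"; effect size 0.314, read as Cohen's f; two groups, two times. The correlation between times is not stated; 0.5 is assumed.

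- Noncentrality for the group-by-time interaction: λ = f²·N·m/(1−ρ) = 0.314² × 22 × 2/0.5 = 8.68, with 1 and 20 degrees of freedom. Power is 0.800, so 22 reproduces.
- Attrition: 22/0.8 = 27.5, rounded up to 28; 22 × 1.2 = 26.4, rounded up to 27. The article gives 27 in total and 14 per group (28).

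The inflation treats lost patients as not analysed, which fits a completers analysis but does not prove one.

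**3. Possible bias if withdrawn patients are not measured**

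The document gives none of the inputs here; all are assumptions. Suppose there is no true effect, the sickest fraction q of an arm is withdrawn, and the health variable has correlation r with the change score. The mean change among those who remain shifts by

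b(q) = r·φ(z)/(1−q), where z is the (1−q) quantile of the standard normal,

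and the bias is b(q in EXP) − b(q in CON). For q = 0.20 and r = 0.5: z = 0.842, φ = 0.280, so b = 0.5 × 0.280/0.80 = 0.175 SD. Simulation (8,000 trials per setting, 14 per arm, t test on change) gave:

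| Withdrawn, EXP v CON | r | Bias towards EXP (SD of change) | Type I error |
|---|---|---|---|
| 20% v 20% | 0.5 | 0.00 | 4.9% |
| 20% v 0% | 0.5 | 0.18 | 7.1% |
| 30% v 10% | 0.3 | 0.09 | 5.8% |
| 30% v 10% | 0.5 | 0.15 | 6.3% |
| 40% v 0% | 0.3 | 0.19 | 7.0% |
| 40% v 0% | 0.5 | 0.32 | 10.3% |

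For scale, the planned effect in SDs of change at ρ = 0.5 is √(4 × 0.314² × 2/0.5) = 1.256. A bias of 0.18 is 0.18/1.256, about 14% of it.

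**4. Power at the plan's own effect size**

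All randomised patients measured (14 v 14): 0.892. Balanced loss (11 v 11): 0.800. Uneven loss (9 v 13): 0.787. All loss in EXP (8 v 14): 0.769. Where the losses fall matters little for power; the concern is bias.

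**The case against.** Several objections have force.

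- **Only one row of five is arm-specific.** A reader might infer that the withdrawal criteria as a whole act differently by arm. The wording does not support that. Longer illnesses, malignancy and cardiovascular events remove patients from both arms. Exertion could make event rates differ, but that is a possibility, not something the article says.
- **The authors may have meant the intervention period.** Row 1 could then apply to both arms. The text does not say so, and CON has nothing to continue.
- **A completers analysis is not stated.** A reader might conclude that the plan analyses completers and that its intention-to-treat label is untrue. The article does not say that withdrawn patients go untested, and missing-data handling may sit in a full protocol or SAP that is not shown. Two times, partial eta-squared and SPSS make a repeated-measures ANOVA the likelier reading, and that would drop anyone without a 12-week value. It remains an inference.
- **The bias cannot be put in score units.** It is tempting to take the pooled SD from the quoted data, √((151.67² + 83.09²)/2) = 122.3, assume 3 of 14 EXP patients withdrawn with scores 0.5 to 1.0 SD worse, and report 3/14 × 0.5 × 122.3 = 13 to 3/14 × 1.0 × 122.3 = 26 units. The planned contrast is group by time, and a withdrawn patient's baseline drops out too, so a stable deficit cancels. Only a difference in change biases the result.
- **The 14-day and 3-week rows overlap but do not contradict each other.** One concerns interrupted training, the other acute illness and its timing.

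What remains is that study withdrawal for health reasons, partly specific to one arm, stands beside an intention-to-treat statement with nothing to connect them. A later SAP could not recover assessments that were never made.

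**Conclusion.** The point holds in limited form. Followed as written, Table 1 takes randomised patients out of the study for health reasons, and row 1 can by its wording do so only in EXP. The EXP-only part is narrow: illness of roughly 15 to 21 days that ends early enough, and trauma that stops training. The article does not reconcile this with its intention-to-treat statement.

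The consequence is conditional. If withdrawn patients are not assessed at 12 weeks, the primary contrast can favour EXP. Its size cannot be derived from the document. Under the assumed settings with unequal withdrawal it ranges from 0.09 to 0.32 SD of the change score, with type I error from 5.8% to 10.3%, and it vanishes when withdrawal is equal in the two arms. It is modest unless withdrawal is both clearly unequal and prognostic. The documents do not support the claims that all the criteria are asymmetric or that a completers analysis is definitely planned.

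**What to change.** 1. Reconcile Table 1 with the intention-to-treat statement by separating discontinuation of the intervention from withdrawal from the study, so that only withdrawn consent ends data collection.
2. Seek the 12-week and 6-month assessments in every randomised patient who consents and is able, by the same rule in both arms, and analyse each in the group assigned.
3. Use a likelihood-based mixed model with all available visits (baseline, 12 weeks, 6 months). On baseline and 12 weeks alone, such a model does not recover patients who lack the 12-week value, because they have no post-baseline data. Obtaining the measurement matters more than the choice of model.
4. Add one sensitivity analysis that assumes worse outcomes for those without a 12-week value.
5. The authors should reconcile the 14-day and 3-week rows and say to which arm each applies. No clinical threshold is proposed here.

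The cost is a minor amendment and a few extra assessments at visits already planned. The estimate will be somewhat diluted by patients who stopped training. The change must come before assessments are lost.

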### Procedures

Throughout the experiment, testing procedures will be conducted in the same facility, by the same researchers, with the same equipment at a similar time of the day. Testing will be performed on non-dialysis day. Finally, the risks and benefits will be explained to each participant prior to enrollment in the study. The risks of study participation are associated with possible deterioration in health status due to physical exertion. However, there will be adequate rest between each physical performance test and physical exertion during dialysis will be adapted to individual abilities with continuous monitoring of hemodynamic status and subjective exertion throughout the dialysis procedure. There will be full coverage with physician presence in research facilities.

#### Study Interventions and Protocol

After the screening, recruitment, and baseline measurements, the patients will be randomized using sealed envelopes in 1:1 ratio into two groups:

– combined cognitive and exercise training (EXP) group and– control (CON) group

The EXP group will first exercise during dialysis (three times a week; 12 weeks) for ~30 min on a customized ergometer. They will start with a 3-min warm-up, and then, the resistance will be implied to each individual according to the rate of perceived exertion of 4th to 5th grade on a 10-grade Borg scale (Bogataj et al., 2020). After a break, they will be given tablets in order to play »cognitive stimulation games« on a CogniFit platform (~30–45 min). CogniFit “brain training” requires patients to repeatedly solve cognitively challenging tasks that target specific cognitive areas. These cognitive tasks are presented in the form of colorful, visually appealing “mini-games” to promote fun and enjoyment, thereby increasing motivation and engagement. The CogniFit platform offers a wide range of games (e.g., Jigsaw, Mandala, Sudoku, Puzzles, Word Quest, Piece Making, Tennis Bowling, and Line Changer, etc.). The difficulty level of the “brain exercises” automatically adjusts to the patient’s abilities as they practice and train. The cognitive areas targeted are: memory, reasoning, coordination, and attention with their subcategories. The training will be performed by a qualified kinesiologists (a professional coach experienced in prescribing and guiding the intradialytic exercise) and by a clinical psychologists with experience in cognitive testing of chronic patients. The CON group will receive standard HD care.

Graphically we present the study design in Figure 1. We plan to repeat the measurements 6 months after the end of the intervention to measure the longer-term retention effect of intervention.

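### Baseline Alertness is adjusted for only if the arms look unmatched; with about 28 patients and no balancing of allocation stated, it should be a covariate in every case

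*Protocol article*

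**What the plan says.** **Allocation** (Study Interventions and Protocol): "After the screening, recruitment, and baseline measurements, the patients will be randomized using sealed envelopes in 1:1 ratio into two groups". The article gives the device, the ratio and the timing. It names no strata, blocks or minimisation factors, and it does not say that there are none.

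**Size** (Statistical Methods Including Sample Size Calculation): "A sample size of 22 participants was calculated", and then "Allowing for a 20% attrition rate, a total number of 27 participants is required, with 14 participants assigned to each group".

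**Analysis** (same section): the default is a mixed general linear model with group and time (baseline, 12 weeks) as factors. ANCOVA with the baseline measurement as covariate replaces it only "in the case of unmatched baseline means". The article gives no threshold for unmatched and names no other covariate.

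**Motivation** (Introduction): the earlier 20-patient pilot in haemodialysis is said to justify "larger randomized interventional studies with a better balance of confounding factors in study groups".

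**The concern.** In a trial this small, chance can leave the arms visibly apart at baseline on the primary score. With two time points, the group-by-time interaction is a comparison of mean change between arms. Patients who start slow tend to move back towards the mean whatever they receive. If the exercise arm happens to start slower, its change looks better than the intervention made it, and the reverse holds if it starts faster.

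ANCOVA removes this shift, but the plan brings it in only after inspection of the baseline means. In every trial where the switch is not made, the shift stays in the primary estimate and precision is given away. The readers of a single small trial would then have trouble telling a treatment effect from a baseline difference.

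**Working it through.** **Inputs from the Statistical Methods section.** Alertness before treatment 376.91 (SD 151.67) and after 302.64 (SD 83.09), from the cycling group of the cited study; 14 per group; effect size 0.314; alpha 0.05; power 0.80. The article gives no unit, and I read the scores as reaction times in ms. The change is 376.91 − 302.64 = 74.27. It is a within-group change, used here only as a yardstick.

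**Assumption.** The article gives no correlation ρ between visits. I take 0.5 to 0.7.

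**1. The plan's sample size.** For the interaction with 2 groups and 2 times, reading 0.314 as Cohen's f, λ = f²·N·2/(1 − ρ). With N = 22 and ρ = 0.5, λ = 0.0986 × 22 × 2/0.5 = 8.68 on 1 and 20 df, which gives power 0.800. The 22 reproduces. Attrition: 22/0.8 = 27.5, so 28, which matches 14 per group.

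**2. Chance gap in baseline Alertness.** SD of the gap = 151.67 × √(2/14) = 57.3 ms, or 0.378 SD.
- P(gap > 74.27 ms): 74.27/57.3 = 1.30, two-sided tail 19.5%. In SD units the limit is 74.27/151.67 = 0.49.
- P(gap > 0.75 SD) = 4.7%; P(gap > 1 SD) = 0.8%.
- With 11 completers per arm the SD is 64.7 ms, and the first probability is 25%.

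**3. Would the switch catch it?** If unmatched were judged by a 5% test (my assumption), the gap would have to exceed about 1.96 × 57.3 = 112 ms. A 74 ms gap would not trigger ANCOVA.

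**4. Shift in the default contrast.** Given a baseline gap D, the contrast of changes moves by (β − 1)·D, where β = ρ·SD₂/SD₁.

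| Follow-up SD | ρ | 1 − β | SD of shift (× 57.3) | Shift at D = 74 ms |
|---|---|---|---|---|
| Equal to baseline | 0.5 | 0.50 | 29 ms | 37 ms |
| Equal to baseline | 0.7 | 0.30 | 17 ms | 22 ms |
| 83.09 | 0.5 | 0.726 | 42 ms | 54 ms |
| 83.09 | 0.7 | 0.617 | 35 ms | 46 ms |

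In simulation with equal SDs and no treatment effect, the change comparison rejects in about 5% of all trials. Among trials with a gap above 0.5 SD it rejects in about 11% (ρ = 0.5) or 9% (ρ = 0.7).

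**5. Precision per patient.**
- Equal SDs: ANCOVA/change variance = (1 − ρ²)/(2(1 − ρ)) = (1 + ρ)/2 = 0.75 to 0.85, so 15 to 25% lower.
- Plan's SDs, ρ = 0.5: change variance 23004 + 6904 − 12602 = 17306; ANCOVA 6904 × 0.75 = 5178; ratio 0.30.
- Plan's SDs, ρ = 0.7: 29908 − 17643 = 12265; 6904 × 0.51 = 3521; ratio 0.29.

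ANCOVA pays a mean variance inflation of 1.04 for chance imbalance at this size. After that the gain is about 12 to 22% with equal SDs (0.85 × 1.04 = 0.88; 0.75 × 1.04 = 0.78) and still about 70% with the plan's SDs.

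**6. What balanced allocation would add.** Two strata split at the median of baseline Alertness cut the SD of the gap from 57 to about 38 ms (lognormal simulation). The chance of a gap above 74 ms falls from 20% to about 5%. Once ANCOVA is used, the mean variance inflation falls only from 1.04 to 1.02, about 2%.

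**The case against.** **Silence is not a statement.** Sealed envelopes are compatible with strata or blocks, and a journal article may leave these to the full protocol. A reader might infer that allocation is unstratified from a single stack of envelopes; the text does not say so. This stands. It leaves the analysis rule untouched, because that rule is written out.

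**No contradiction with the Introduction.** A reader might infer that the plan breaks its own promise of balance. It asks for larger and better-balanced studies, and promises no stratification. Against the pilot's arms of 6 and 7, the SD of a chance gap falls from √(1/6 + 1/7) = 0.56 SD to 0.38 SD. This stands.

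**Large imbalances are not likely for any one factor.** A gap above half the yardstick, 37 ms, arises in 52% of trials, but that is only 0.24 SD. A reader might add frailty: with 13 of 28 frail (the article's 46%), a split of 9 to 4 or worse has probability 13%, and 8 to 5 or worse 45%. But 7 to 6 is the best split possible. The 46% also describes haemodialysis patients in general, whereas this trial takes stable patients who walk independently. Frailty in the enrolled sample is unknown. This stands.

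**ANCOVA is already in the plan.** True, and the largest gaps are the ones most likely to trigger it. The switch still leaves moderate gaps to the change contrast, and when it is not made the precision is lost as well. Here the objection fails.

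**The test is valid.** Agreed. ANCOVA holds its level at any gap, and the change comparison is conservative when gaps are small. A switch made on baseline data alone should therefore not raise the overall error rate.

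**Conclusion.** The point holds as a weakness of the stated analysis rule. It is neither a flaw in validity nor proof of a poor allocation method. With 14 per arm and the plan's baseline SD, about one trial in five starts with an Alertness gap as large as the change used for planning. The default contrast then carries a shift of 22 to 54 ms at such a gap, unless the switch happens to be made.

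The 20% rests on the cited study's SD carrying over to these patients and on a normal approximation. The shift and precision figures rest on the assumed correlation and on the follow-up SD. The 83.09 comes from a treated group, and the control arm's follow-up SD is unknown, so the equal-SD figures are the cautious end. Both ends favour unconditional adjustment. The case for changing the allocation is much weaker, about 2% in variance once ANCOVA is used.

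**What to change.** In Statistical Methods Including Sample Size Calculation, delete the conditional clause and state that the primary analysis is ANCOVA of the 12-week Alertness score on group, with baseline Alertness as covariate, whatever the observed baseline means. Keep the group-by-time model as supportive if wanted. Baseline Edmonton Frail Scale may be named in advance as a second covariate. Nothing in the article shows that it predicts 12-week Alertness beyond baseline Alertness, so this is optional.

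The cost is an edit of a sentence or two and one or two degrees of freedom. It needs no extra patients, visits or tests, since both measures are taken at baseline.

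For allocation, state whether the full protocol stratifies. If it does not, the sponsor may balance on baseline Alertness, at a cut fixed before the first allocation, by stratified blocks or by minimisation with a random element. This takes a little more set-up and brings a modest further gain, mainly in how comparable the arms look.
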